#### Serious Adverse Event (SAE)

Any AE (whether or not considered related to the investigational product) that results in any of the following outcomes is defined as an SAE.

- 1) Death (i.e., results in death from any cause at any time)
- 2) Life-threatening event (i.e., the subject was, in the view of the investigator, at immediate risk of death from the event that occurred). This does not include an AE that, if it occurred in a more serious form, might have caused death.
- 3) Persistent or significant disability or incapacity (i.e., substantial disruption of one's ability to carry out normal life functions).
- 4) Hospitalisation: regardless of length of stay, even if the hospitalization is a precautionary measure for continued observation.  
Hospitalisation (including inpatient or outpatient hospitalization for an elective procedure) for a pre-existing condition that has not worsened

unexpectedly does not constitute a serious AE.

- 5) An important medical event (that may not cause death, be life threatening, or require hospitalization) that may, based upon appropriate medical judgment, jeopardize the subject and/or require medical or surgical intervention to prevent one of the outcomes listed above. Examples of such medical events include allergic reaction requiring intensive treatment in an emergency room or clinic, blood dyscrasias, or convulsions that do not result in inpatient hospitalization.
- 6) Results in a congenital anomaly or birth defect.

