**HIV specific risks:** There is a hypothetical risk of any vaccine causing a rise in viral load in HIV positive individuals. However in individuals established on ARVs this has not been seen with MVA vaccines [30]. A small number of HAART naïve individuals in Africa have also been vaccinated with a recombinant MVA with no significant or sustained rise in viral load or fall in CD4 count [32]. Volunteers will be monitored clinically together with regular monitoring of CD4 counts and viral loads. However, observed changes in CD4/viral load will have to be carefully interpreted in the context of a well-described natural fluctuation in these parameters. Any significant changes in these will be communicated to the volunteer's lead HIV physician forthwith and BHIVA guidelines (BHIVA treatment guidelines 2005) will be followed to determine the need to commence ARVs.

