### Definitions

#### Adverse Event

An AE is any untoward medical occurrence, including a dosing error, which may occur during or after vaccination.

The AE may or may not have a causal relationship with vaccination as indicated by physical signs, symptoms, and/or clinically significant laboratory abnormalities that occur. The definition includes intercurrent illnesses, injuries, exacerbation of pre-existing conditions, and events occurring as a result of product misuse or overdose.

A change in a laboratory variable is considered an AE if it leads to a change in the subject's functional status or if it is considered by the attending physician to be clinically significant. The following laboratory studies will be monitored during the course of this study (as previously outlined): full blood count (FBC), urea, creatinine, ALT, total bilirubin, albumin, alkaline phosphatase, sodium and potassium.

Adverse events will be graded and reported as detailed below.

Expected local reactions to the vaccine will not be recorded as an adverse event, but will be recorded on the CRFs. These include:

- Redness
- Swelling
- Pruritus
- Scaling
- Localised pain

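### The SAE definition exempts any admission for a pre-existing condition that has not worsened 'unexpectedly', so an unplanned admission for HIV worsening judged expected could go unreported as serious

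*Protocol*

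**What the plan says.** All references are to the Protocol.

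- **Section 8, Serious Adverse Event (SAE), opening.** An AE, whether or not considered related to the product, "that results in any of the following outcomes is defined as an SAE".
- **Same definition, item 4.** The general criterion is broad: "Hospitalisation: regardless of length of stay, even if the hospitalization is a precautionary measure for continued observation". An exemption follows for hospitalisation, with elective procedures named in a parenthesis, "for a pre-existing condition that has not worsened" "unexpectedly does not constitute a serious AE". The last two quotes are parts of one continuous sentence.
- **Section 8, Adverse Event.** Worsening of an existing illness is an AE, with no test of whether it was expected: "The definition includes intercurrent illnesses, injuries, exacerbation of pre-existing conditions".
- **Section 1, Potential risks, HIV specific risks.** "There is a hypothetical risk of any vaccine causing a rise in viral load in HIV positive individuals". The same paragraph provides for regular CD4 and viral load monitoring and says that changes must be read against natural fluctuation.
- **Section 8, SAE Reporting and Local Safety Monitor.** The 24-hour report, the onward notification to the sponsor and ethics bodies, and the monitor's real-time review all attach to SAEs.

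**The concern.** Seriousness describes the outcome of an event. Expectedness is a separate judgement, needed to decide whether a serious reaction is a SUSAR. Item 4 mixes the two: for a pre-existing condition, an admission is serious only if the worsening was unexpected.

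In a trial of healthy volunteers this would rarely matter. Here every subject enters with HIV, and half are untreated. Section 5 says that all volunteers are vaccinated and none randomised, so there is no concurrent unvaccinated group against which to test a judgement that one subject's worsening was simply the course of the disease. If that judgement is made, item 4 takes the admission out of the hospitalisation criterion and so, unless another criterion applies, out of expedited reporting and the monitor's review. The primary objective is safety, so the SAE count should not rest on an undefined term.

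**Working it through.** The Protocol gives no SAE rate and no sample size calculation, so there is no stated figure to reproduce. The check is a reading of the text, followed by a small calculation for scale.

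**1. What the exemption covers.** The elective procedure appears in a parenthesis that begins with *including*. It is an example, so unplanned admissions for a pre-existing condition are also covered.

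**2. What the test is.** Four cases follow from the sentence:

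| Admission for a pre-existing condition | SAE under item 4? |
|---|---|
| No worsening, elective | No |
| No worsening, unplanned | No |
| Worsened, judged unexpected | Yes |
| Worsened, judged expected | No |

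The last row is the problem. The Adverse Event definition counts that worsening as an AE whether or not it was expected, and the opening of the SAE definition disregards relatedness. Expectedness enters only through this exemption, and the Protocol does not say when worsening is expected.

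**3. Whether HIV is a pre-existing condition.** Yes, by eligibility (section 4): Group 1 was diagnosed at least 6 months earlier and Group 2 at least 12 months earlier. That is 12 + 12 = 24 of 24 subjects. No sentence takes HIV out of the exemption.

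**4. What still captures the event.** It remains an AE, recorded from Day 0 to the end of the trial. It can be serious under item 1, 2, 3 or 5 (death, threat to life, disability, important medical event). CD4 and viral load are measured at screening and at every scheduled blood visit (Table 3).

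**5. Scale, as illustration only.** Exact (Clopper-Pearson) two-sided 95% intervals use beta quantiles: lower limit B(0.025; x, n − x + 1), upper limit B(0.975; x + 1, n − x). For x = 0 the upper limit reduces to 1 − 0.025^(1/n).

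| | SAE proportion | 95% interval |
|---|---|---|
| 0/24 | 0% | 0 to 14.2% |
| 1/24 | 4.2% | 0.1 to 21.1% |
| 0/12 | 0% | 0 to 26.5% |
| 1/12 | 8.3% | 0.2 to 38.5% |

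The Protocol gives no rate for such admissions. If the true proportion of subjects affected were p, the chance of at least one among 24 would be 1 − (1 − p)^24. For assumed p of 1%, 2%, 5% and 10% this is 21%, 38%, 71% and 92%. In one group of 12 it is 11%, 22%, 46% and 72%. These are chances that such an admission occurs, not that it is exempted.

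**The case against.** The strongest objection is that the scenario needs a strained judgement. Entrants are healthy adults with CD4 above 300 and no AIDS-defining illness; Group 2 must also have had a stable regimen and undetectable virus for 12 months. In such people an HIV-related admission would often be called unexpected and would stay an SAE. The natural fluctuation mentioned under HIV specific risks concerns laboratory values, not admissions. This largely stands. It makes the problem less likely, above all in Group 2, but leaves the decision to an undefined word.

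A second objection is that the event is not lost, for the reasons in step 4 of the working, and that an admitted subject would ordinarily also be graded severe. This stands too, and it confines the point to SAE classification and reporting. Item 5 is an incomplete remedy, because it again rests on judgement.

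A reader might infer three stronger things that the document does not support:

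- **That the trial would miss the HIV risk it exists to detect.** The Protocol calls that risk hypothetical, words it as a rise in viral load, and measures viral load and CD4 directly.
- **That a Koch reaction or tuberculosis would be exempted in the same way.** Section 1 describes a Koch reaction as immunopathology from an exaggerated immune response after immunisation. That is a new event, not a pre-existing condition that ran its expected course.
- **That the halting rule is disabled.** The halt needs a SUSAR, hence a suspected reaction. An admission put down to natural HIV progression would be judged unrelated and would not become a SUSAR even if counted as serious.

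**Conclusion.** The point holds as a defect in the wording of a safety definition. Item 4 lets an undefined expectedness judgement decide seriousness, is not limited to planned or elective admissions, and applies on its face to a condition that all 24 subjects have. An unplanned admission for HIV worsening judged expected could be left out of the SAE count, the 24-hour report and the Local Safety Monitor's review.

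The conclusion assumes a literal reading of the sentence, an investigator who regards the worsening as expected (most plausible in untreated Group 1), and an event that meets no other seriousness criterion. How often this would happen cannot be worked out from the Protocol. The 0/24 against 1/24 comparison shows what one reclassified event does in any trial of this size; it is not evidence of a bias of that size. No stated figure is wrong. The change is worth making because safety is the primary objective and the correction is cheap.

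**What to change.** In item 4 of the SAE definition, delete the word *unexpectedly* and limit the exemption to planned or elective admissions for a pre-existing condition that has not worsened since Day 0. An unplanned admission for worsening HIV is then an SAE under the hospitalisation criterion, whatever view is taken of its cause or predictability. Add that expectedness is used only to classify SUSARs.

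The cost is one sentence, plus the sponsor agreement and ethics approval that the Protocol Deviations section requires for a change. The downside is that a few admissions from natural HIV progression will be reported as SAEs judged unrelated. The change needs no new visits or tests and leaves the sample size as it is.

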### **Adverse Events Assessment**

For every adverse event (AE), an assessment of the relationship of the event to the administration of the vaccine will be undertaken. An intervention-related AE refers to an AE for which there is a probable or definite relationship to administration of a vaccine. The investigator will make interpretation of the causal relationship of the intervention to the AE in question. This interpretation will be based on the type of event, the relationship of the event to the time of vaccine administration, and the known biology of the vaccine therapy. The following are guidelines for assessing the relationship of administration of one of the study vaccines to the AE

#### **1. NO RELATIONSHIP:**

- No temporal relationship to study product; and
- Alternate aetiology (clinical state, environmental or other interventions); and
- Does not follow known pattern of response to study product

#### **2. POSSIBLE:**

- Reasonable temporal relationship to study product; or
- Event not readily produced by clinical state, environmental or other interventions; or
- Similar pattern of response to that seen with other vaccines

#### **3. PROBABLE:**

- Reasonable temporal relationship to study product; and
- Event not readily produced by clinical state, environment, or other interventions or
- Known pattern of response seen with other vaccines

#### **4. DEFINITE:**

- Reasonable temporal relationship to study product; and
- Event not readily produced by clinical state, environment, or other interventions; and
- Known pattern of response seen with other vaccines

Every AE observed or reported from the day of injection [Day 0] through to the end of the trial (twelve months after injection) will be recorded on the CRF.

All AEs will be followed until resolution of the symptom or laboratory change occurs, or until a non-study related causality is assigned.

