#### **End of trial:**

The trial ends when the last volunteer has completed their last (twelve month) follow-up visit.

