**Table 2: Illustration of sequential events (screening and subsequent follow-up):**

| Visit number              | 1         | 2              | 3–8 | 9   | 10  | 11  | 12             | 12.1 ^ | 13–18            | 19  | 20  | 21  | 22  |
|---------------------------|-----------|----------------|-----|-----|-----|-----|----------------|-------------------|------------------|-----|-----|-----|-----|
| Day                       | Screening | 0              | 1–6 | 7   | 28  | 84  | 168
(+/-14) | 168-350           | 1–6 ◇ | 7   | 28  | 84  | 168 |
| Medical history           | √         | (√)            | (√) | (√) | (√) | (√) | (√)            | (√)               | (√)              | (√) | (√) | (√) | (√) |
| Physical examination      | √         | (√)            | (√) | (√) | (√) | (√) | (√)            | (√)               | (√)              | (√) | (√) | (√) | (√) |
| Vital signs °  | √         | √              | √   | √   | √   | √   | √              | √                 | √                | √   | √   | √   | √   |
| Urinalysis                | √         | √ † |     |     |     |     | √ † | √ †    |                  |     |     |     |     |
| Chest x-ray #  | √         |                |     |     |     |     |                |                   |                  |     |     |     |     |
| Venepuncture              | √*        | √*             |     | √*  | √*  | √*  | √*             | √*                |                  | √*  | √*  | √*  | √*  |
| Vaccination               |           | √              |     |     |     |     | √              | √                 |                  |     |     |     |     |
| Injection site inspection |           | √              | √   | √   | √   | √   | √              | √                 | √                | √   | √   | √   | √   |
| Adverse events documented |           | √              | √   | √   | √   | √   | √              | √                 | √                | √   | √   | √   | √   |

(√) If considered necessary (emphasizing any acute complaints)

^ Visit 12.1 is only required if a subject has been for their 6 month visit but was not revaccinated because the 6 month visit was prior to the second vaccination amendment

° Temperature (°C), blood pressure (mmHg), pulse rate (beats/minute)

† Women only for pregnancy test

# Performed if no available CXR within the last 3 months

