\* See table 3 for exact blood tests performed at each visit

◇ Note that the days from this point on are shown as days after the second vaccination

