**Booster vaccination:**

- For Group 1, if Day 168 visit is before Protocol 2.0 amendment, the second vaccination will be given between days 168-350 (visit 12.1). However, before the subject receives the second vaccination, all inclusion and exclusion criteria except number 5 (Prior receipt of a recombinant MVA or Fowlpox vaccine) will be reviewed to check if the subject is still eligible to receive the vaccine. At this additional visit, 20 ml of blood will be collected to perform FBC, Biochemistry, CD4 and VL tests. Urinalysis, to exclude glycosuria and significant proteinuria will be performed. If any exclusion criterion are met except number 5, the subject will not be revaccinated.
- For Group 2, the second vaccination will be given at Day 168 (+/- 14 days)
- A photograph of the vaccination site will be taken after revaccination. The subject will only be identifiable by a unique study number.

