**Subsequent follow-up visits**

Volunteers will be reviewed at 28 (+/- 4 days), 84 (+/- 7 days) and 168 days (+/- 14 days) after the second vaccination.

- An interim history will be taken and, if considered necessary a physical examination emphasizing any acute complaints will be performed.
- Vital signs will be checked and documented
- The injection site will be inspected and the largest diameter of any hardness or redness present, as well as the degree of pain reported for the time of the visit will be documented into the CRF.
- Solicited adverse events (local and general) that may have occurred since the volunteer was seen on day 7 post second vaccination will be documented in the CRF.
- Approximately 32-42 ml of blood will be collected for exploratory immunology, viral load and CD4 cell count on days 28, 84 and 168 after the second vaccination. On day 84 after the second vaccination only, haematology and biochemistry will also be performed; therefore, the blood volume will be 40-50 ml.

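### The twelve-month limit on AE recording does not fit a Group 1 second dose given after about Day 197, and it contradicts the protocol's own post-boost visit schedule

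*Protocol*

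**What the plan says.** Five parts of the protocol bear on this.

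- **Section 8, Adverse Events Assessment** (closing paragraphs), gives the recording period for the CRF: "Every AE observed or reported from the day of injection [Day 0] through to the end of the trial (twelve months after injection". Injection is in the singular and is tied to Day 0.
- **Section 3, End of trial:** "The trial ends when the last volunteer has completed their last (twelve month) follow-up visit".
- **Section 5, Booster vaccination.** For Group 1 subjects whose Day 168 visit came before the second-dose amendment, "the second vaccination will be given between days 168-350 (visit 12.1". The Table 2 footnote limits that visit: "Visit 12.1 is only required if a subject has been for their 6 month visit but was not revaccinated" because the amendment was not yet in place. For the other arm: "For Group 2, the second vaccination will be given at Day 168 (+/- 14 days".
- **Section 5, Subsequent follow-up visits** (after dose 2): "Volunteers will be reviewed at 28 (+/- 4 days), 84 (+/- 7 days) and 168 days (+/- 14 days) after the second vaccination".
- **Section 5, Table 2.** The row "Adverse events documented" is ticked at every visit from 2 to 22. For visits 13 to 22 the footnote says: "Note that the days from this point on are shown as days after the second vaccination".

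The primary objective (section 2) and primary outcome (section 7) are the safety of two injections, with AE data as the endpoint.

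**The concern.** Two rules describe the period over which the primary endpoint is collected. One stops twelve months after Day 0. The other runs to 168 (+/-14) days after dose 2, whenever dose 2 was given. They agree for a subject boosted at visit 12. They diverge for a subject boosted late at visit 12.1.

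If site staff or the analyst follow section 8, later AEs after the second dose drop out for some Group 1 subjects and for nobody in Group 2. If they follow Table 2, those AEs are collected but lie outside the stated recording period, and whether they are reported is left to discretion. In either case the observation time behind the dose 2 AE frequencies is not fixed by the protocol.

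**Working it through.** **Inputs.** AE limit: twelve months after Day 0, taken as Day 365 (section 8). Dose 2 at visit 12: Day 168 +/-14 (Table 2 and Booster vaccination). Dose 2 at visit 12.1: Days 168 to 350 (Booster vaccination). Last visit: 168 +/-14 days after dose 2 (Subsequent follow-up visits). The ten post-boost visits are on Days 1 to 6, 7, 28, 84 and 168 after dose 2 (Table 2).

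**Step 1. Where twelve months is right.** For a boost at visit 12, the nominal last visit is 168 + 168 = Day 336. The latest is 168 + 14 + 168 + 14 = Day 364. The twelve-month figure therefore reproduces for Group 2 and for any Group 1 subject boosted at visit 12.

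**Step 2. Where it fails.** For a boost on Day 350, the last visit is 350 + 168 = Day 518, or 350 + 182 = Day 532 at the end of the window. At 365/12 days per month that is 17.0 to 17.5 months.

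**Step 3. Days lost under a literal reading of section 8.** For a boost on day b, days lost = max(0, b + 168 - 365) = max(0, b - 197). A post-boost visit on day v is lost if b + v > 365.

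| Boost day | Nominal last visit | Days lost of 168 | Post-boost visits lost |
|---|---|---|---|
| 197 | 365 | 0 | none |
| 198 | 366 | 1 (0.6%) | Day 168 |
| 240 | 408 | 43 (25.6%) | Day 168 |
| 281 | 449 | 84 (50.0%) | Day 168 |
| 282 | 450 | 85 (50.6%) | Days 84, 168 |
| 300 | 468 | 103 (61.3%) | Days 84, 168 |
| 338 | 506 | 141 (83.9%) | Days 28, 84, 168 |
| 350 | 518 | 153 (91.1%) | Days 28, 84, 168 |

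The Day 7 visit after a Day 350 boost falls on Day 357, so the Day 1 to 7 visits are always inside the limit.

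**Step 4. How much of the boost window is affected.** The window has 350 - 168 + 1 = 183 permitted days. Of these, 350 - 198 + 1 = 153 lose some follow-up, and 350 - 282 + 1 = 69 lose more than half. These count calendar days, not subjects.

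**Step 5. Sensitivity.** With the last visit moved by 14 days either way, loss begins after Day 183 to 211 and passes half after Day 274 to 288. With twelve months taken as 360 to 366 days and the visit on its nominal day, loss begins after Day 192 to 198.

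**Step 6. Counting from dose 2 instead.** Twelve months after the second injection lies 365 - 168 = 197 days beyond the nominal last visit. No visit exists there, and the last visit would still not be a twelve-month visit. Neither reading of injection reconciles the text.

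**The case against.** The strongest reply is that twelve months is only a label. Section 3 ends the trial when the last volunteer completes the last visit, and section 8 runs to the end of the trial with the twelve months in parentheses. Table 2 requires AE documentation through visit 22, the visit text after dose 2 requires solicited AEs in the CRF, and section 8 opens by covering all AEs after vaccine administration. No sentence tells staff to stop at Day 365. The analysis is descriptive only (section 10), and no safety comparison between doses or groups is specified; the stated group comparison concerns immune response.

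Most of this stands, and it rules out three stronger conclusions that a reader might draw:

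- **That most dose 2 follow-up is lost for everyone boosted after Day 197.** Loss starts there at a single day and passes half only after about Day 281.
- **That the trial, and so the data, certainly stops at twelve months.** Section 3 ties the end to the last visit, and Table 2 still calls for AE documentation.
- **That dose 2 AEs will be under-counted in the no-ARV group.** That follows only if section 8 is applied literally.

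The reply does not remove the contradiction. Section 8 is where the protocol states a recording period for every AE, and it gives a number that is wrong for part of Group 1. The post-boost visit text speaks of solicited events, so the requirement for other AEs at those visits rests on a row in Table 2.

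**Conclusion.** The point holds as an internal contradiction about the observation period of the primary endpoint. It is not an established loss of data. It affects Group 1 subjects boosted at visit 12.1 after about Day 197: at most 12 of the 24, with the actual number not stated. Under a literal reading of section 8, the loss runs from 1 day to 153 of 168 days, and from one to three of the ten post-boost visits. Early reactogenicity through Day 7 after dose 2 is never lost.

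This rests on Day 365 as twelve months, nominal visit days, and the Day 168 (+/-14) rule for Group 2. The Rationale allows roughly 6 to 12 months between doses in the ARV arm as well; a Group 2 boost given on that basis after about Day 197 would meet the same problem.

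The text is wrong as written and should be corrected, because it concerns the primary endpoint and the correction is nearly free.

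**What to change.** 1. **Section 3, End of trial.** Delete the twelve-month label and define the end of trial as the last subject's final scheduled visit.
2. **Section 8, Adverse Events Assessment.** Record every AE from Day 0 through the later of (a) twelve months after Day 0 and (b) the Day 168 (+/-14) visit after the second injection. Taking the later date matters: ending recording 168 days after the last injection received would cut the window to about six months for Group 1 subjects who decline the booster, as the Rationale allows.
3. **If AEs are summarised by dose,** use the same post-dose window for each dose, with the number injected at that dose as denominator. Also list AEs that fall between the windows. With 168-day windows and a Day 350 boost, that gap is 350 - 168 = 182 days.

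The cost is an amendment of two sentences, plus a line on reporting if per-dose summaries are made. No visits are added, because Table 2 already schedules them with AE documentation. Where a subject's last visit falls before twelve months, events after it depend on reports reaching the site, as they do under the present text.
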